## Discussion

Pivmecillinam is an excellent choice against urinary tract infections, and has shown to be both safe and effective against UTI [6, 12, 22], with a clear superiority to placebo [12] and superiority to sulftamethiazole [22]. In these days, with the concerning rise of multidrug-resistant bacteria, pivmecillinam has shown to be of an especial advantage; demonstrating low collateral damage (i.e. minor impact on the normal microflora [21], low resistance [3, 9], low selectivity and clonal spread of resistance [11]), as well as indication of clinical and bacteriological effective against ESBL producing Enterobacteriaceae [13, 23]. Hence, there are good evidences backing pivmecillinam as a first line of drug in the treatment of LUTI, as stated in the international guidelines [2], and as long time practiced in the Scandinavian countries.

Ferry et al. [12] have demonstrated that a 7-day regimen is superior to a 3-day regimen against uncomplicated LUTI. However, the current guidelines do not recommend a 7-day therapy, because of the increased risk of side effects (i.e. GI-problems). Nevertheless, there are no data comparing the 3-day vs. the 5-day therapy. With the 5-day therapy possibly to be more effective and with non-significant increased risk of side effects than the 3-day; a 5-day therapy might be a more cost-beneficial duration for the patient in the treatment of uncomplicated LUTI. Thus, with this study we want to strengthen and fill the gaps of evidence in our guidelines.

We have chosen the 400 mg dose *t.i.d.,* since that is the dose we recommend in Denmark; and we believe 200 mg *t.i.d* to be an insufficient dose (i.e. supported by pharmacokinetic mouse models [15] and the recent study from Soraas et al*.* [14]). With this knowledge, we believe it to be unethical of us to use a 200 mg dose, and have therefore excluded a treatment arm with 200 mg.

### Design and definitions

We designed this protocol similarly to previous similar clinical studies on uncomplicated LUTI [12, 22, 24, 25], in order to be able to compare results in the future in a more accurate way. We define uncomplicated LUTI in concordance with the acknowledged definition [1, 26], with one difference; we choose to include post-menopausal women in our study, since we do not necessarily believe them to always be of complicated LUTI. Hence, if a post-menopausal woman has no other complicated conditions (see exclusion criteria) we believe her to be a potential candidate.

### Procedures

We want the inclusion procedures to be as realistic as possible. Therefore, the consulting with the GPs will be changed as little as possible and restricted to the inclusion day. However, patients will be clearly instructed to return to the GP as usual at sign of treatment failure, or if they wish to consult for any other reason.

### Outcomes

The primary outcome we want to focus on is the clinical effect, since that is of most importance to the patient. However, it is important to know that the bacteria disappear and not cause clinical relapses in the future; therefore, we included two follow-up urine sample at day-4 and day-28, respectively.

#### Scientific and societal perspective

This study will give us the knowledge of what drug therapy of pivmecillinam that is most effective and sufficient. If the 5-day therapy will show to be significantly superior to the 3-day regimen, the current guidelines will have to be changed in best interests of the patients. Also through the perspective of the patients, it will be beneficial if the 3-day regimen is proven to be non-inferior to the 5-day regimen (i.e. higher rate of compliance, and less antimicrobial consumption cause less economic and ecological loads), and we can keep using the 3-day regimen in concordance with the principles of evidence-based medicine.

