### Power analyze

We hypothesize that there is a 15% absolute differences in efficacy between the groups, measured in clinical efficacy. We believe there to be an even bigger difference in bacteriological efficacy. Assuming an efficacy of 90 and 75% for 5 days and 3 days therapy, respectively, using a double-sided test with *p* < 0.05, and a statistical power of 0.8, we will need 113 patients in each group for the NTT analysis. With an estimated fall-out rate of app. 30% between each arm; 161 patients per group will need to be included for the PP analysis, and 230 in each group for the ITT analysis. There is a possibility for an interim analysis after 300 included participants, since we cannot reject a possibility for a higher (i.e. 20%) absolute efficacy.

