## Data processing and statistical analysis

The source data is the GP’s and patient’s questionnaires and the diagnostics answers from the microbiological lab at the DCM. All source data will all be stored by the investigator and sponsor, in originals and scanned copies, at the DCM. The collected source data are transferred, logged and processed in the computers of the DCM. Analysis will be made in ITT, PP, and NTT form, respectively. All data will be analyzed coded, and only de-coded after the analysis is done and the analytic results are written in the relevant sections in the future article. The statistical software packages SAS (SAS Institute, Cary, NC) will be used for all analyses. Categorical data will be analyzed using a Fisher’s Exact test.

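### The protocol foresees proof that 3 days is non-inferior to 5 days, but its hypothesis, sample size and named test address only a difference, and no margin is stated

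*Protocol article*

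**What the plan says.** Under Scientific and societal perspective, the protocol article describes two results that would guide practice. If 5 days is significantly better, guidelines should change. Alternatively, "it will be beneficial if the 3-day regimen is proven to be non-inferior to the 5-day regimen", in which case the 3-day course can continue as evidence-based practice.

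The section Power analyze sets the hypothesis: "We hypothesize that there is a 15% absolute differences in efficacy between the groups, measured in clinical efficacy". The calculation takes cure rates of 90% with 5 days and 75% with 3 days, a two-sided 5% level and 80% power. Its result is "we will need 113 patients in each group for the NTT analysis", which is raised to 161 per group for the PP set and 230 for the ITT set.

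Data processing and statistical analysis names one test: "Categorical data will be analyzed using a Fisher’s Exact test". It also says that ITT, PP and NTT analyses will all be made. The article gives no non-inferiority hypothesis, margin or interval rule.

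**The concern.** A test of difference and a claim of non-inferiority answer different questions. Rejecting equality can support superiority of 5 days. Failing to reject it says only that the data do not exclude a zero difference, and they may equally fail to exclude a large deficit with 3 days. Non-inferiority needs a stated largest acceptable deficit and evidence that the true deficit is smaller.

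The article attaches a practice consequence to non-inferiority but fixes its hypothesis, size and named test for a difference. If the trial ends with p above 0.05, nothing stated in the design separates a reassuring result from an uninformative one. A reader who takes the Discussion at its word could treat either as grounds for keeping the shorter course.

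**Working it through.** **1. Reproduce the plan's size.** Inputs from Power analyze: p₁ = 0.90, p₂ = 0.75, two-sided α = 0.05, power 0.80, so z = 1.960 and 0.842. The mean rate is p̄ = 0.825.

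- Without continuity correction: n = [1.960·√(2·0.825·0.175) + 0.842·√(0.90·0.10 + 0.75·0.25)]² / 0.15² = 99.5, so 100.
- With continuity correction: (99.5/4)·[1 + √(1 + 4/(99.5·0.15))]² = 112.5, so 113, which is the stated figure.
- Allowing for 30% loss: 113/0.7 = 161.4 (stated 161) and 161/0.7 = 230.0 (stated 230).

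The sizes are therefore those of a two-sided test for a difference. No margin enters them.

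**2. How often would a real deficit be non-significant?** The true 5-day rate is 90%, and the power of Fisher's exact test is found by summing over all possible outcomes. The 10- and 5-point deficits are assumptions.

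| True rates (5 v 3 days) | 113 per group | 161 | 230 |
|---|---|---|---|
| 90% v 80% | 51% | 33% | 17% |
| 90% v 85% | 85% | 78% | 69% |

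**3. What could the planned sizes show about non-inferiority?** The article gives no margin, so M = 10 points is an assumption. With equal true rates p and one-sided α = 0.025, power = Φ(M/SE − 1.96), where SE = √(2p(1−p)/n).

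Example for n = 113, p = 0.90: SE = √(0.18/113) = 0.0399; 0.10/0.0399 − 1.96 = 0.55; Φ = 0.71.

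| True rate in both arms | 113 per group | 161 | 230 |
|---|---|---|---|
| 90% | 71% | 85% | 95% |
| 80% | 47% | 61% | 77% |
| 75% | 41% | 55% | 70% |

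With an assumed 5-point margin, power is at most 43% at any of the three sizes. For 80% power at equal true rates of 90%, 80% and 75%, a 10-point margin needs 142, 252 and 295 per group, and a 5-point margin needs 566, 1005 and 1178.

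**4. The interval must be matched to the test.** Take 102/113 v 91/113 cured. Fisher's p = 0.058. The difference is 11/113 = 9.7 points, with a Wald 95% interval of 0.6 to 18.9 points. The named test is non-significant, yet the interval excludes zero and contains the 15 points that the trial was sized to detect. Part of this disagreement is Fisher's conservatism, so the example does not by itself show non-significance being taken for non-inferiority. It does show that a plan reporting both must say which governs.

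**The case against.** The strongest reply has four parts.

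- **The phrase is conditional and sits in the Discussion.** It is not a hypothesis, endpoint or decision rule. A reader might infer that the sponsor intends to treat p > 0.05 as non-inferiority, or even equivalence. The article does not say so: it never speaks of equivalence, and Presentation of the results allows for inconclusive findings. This stands. The supported statement is that a null result could be misread, not that it will be.
- **A condensed article may leave a margin and interval rule to an analysis plan that is not shown.** This stands as far as the bare omission goes. It does not answer the conflict within the article, which itself fixes a hypothesis and size for a difference and itself foresees a conclusion that these do not address.
- **Figures at 113 per group alone would overstate the problem.** This stands, and all three planned sizes are shown for that reason. The figures at 230 are in turn a best case. The PP set is defined by having follow-up data, so about 230 − 161 = 69 patients per group in the ITT set would lack some of it.
- **The rest of the plan does not lean one way.** A reader might infer that every other weakness also favours a null result. The documents do not support that. Two co-primary endpoints, three analysis sets and a possible interim analysis could raise the chance of a spurious difference instead.

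**Conclusion.** The point holds in this form: the article foresees a non-inferiority conclusion with a practice consequence, while its stated hypothesis, size and named test are for a difference and no margin or interval rule is given. The missing margin and decision rule are the defect, not the number of patients in every scenario.

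The risk of an uninformative null result is substantial in the smallest set and falls as the analysed number rises. Whether the planned size could support a non-inferiority claim depends on the margin and the true cure rate. For a 10-point margin the answer ranges from poor to good, and for a 5-point margin it is poor throughout. These figures assume a true 5-day rate of 90% in the deficit scenarios, equal true rates in the non-inferiority scenarios, and an outcome for every patient counted. The superiority comparison itself is unaffected.

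**What to change.** 1. Report the risk difference (5-day minus 3-day) with its two-sided 95% confidence interval alongside the planned Fisher test. Use an interval method consistent with that test, or state which of the two governs if they disagree.
2. State that a non-significant difference alone is inconclusive about non-inferiority.
3. Then do one of the following:
   - delete or qualify the non-inferiority wording under Scientific and societal perspective; or
   - fix a justified margin before unblinding, allow the claim only if the upper 95% limit of the risk difference lies below that margin in both the ITT and PP sets, and restate the power at the planned numbers for that margin.

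The first option costs a few sentences and gives up a claim that the stated design cannot support. The second needs a clinical justification for the margin and a short power calculation. It needs more patients only if the restated power proves too low.

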## Conclusion

We believe this study will fill the scientific gaps and provide sufficient evidence for the most efficient dose duration of pivmecillinam against uncomplicated lower urinary tract infections. Thus, strengthening the guidelines for one of the most common community acquired infections in our society.

## Abbreviations

b.i.d: Two times daily
DCM: Department of clinical microbiology
ESBL: Extended Spectrum Beta-Lactamase
GCP: Good clinical practice
GP: General practitioner
ITT: Intention-to-treat
LUTI: Uncomplicated Lower Urinary Tract Infections
NTT: Need-to-treat
PP: Per-protocol
t.i.d.: Three times daily
